**Figure 3 figure3:**
[figure not shown]
Sample size estimation for different scenarios for power and correlation.

We adopted this sample size calculation post hoc after the aforementioned clinically relevant finding. We kept the recruitment of 75 participants but adapted the study post hoc to 3 groups with 25 participants in each. For any significant findings, this post hoc adaptation will be further investigated in the analysis stage by power calculation to assess potential limitations for the main analysis and reporting of results to avoid relying on findings by chance.

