#### Sample Size Calculation

From a pilot study data consisting of 18 participants (8 patients and 10 asymptomatic controls), we found a correlation of 0.37 between the liTr and liMa for the treatment group and an overall correlation of 0.63 for all individuals included in the study [16]. Using these findings, we considered different correlation scenarios between liTr and liMa for a different power of analysis (Figure 3). For a 5% significance level, 90% power, and a correlation of 0.37, we need 76 shoulders. Considering a possible dropout rate of 5%, we need 80 shoulders for the first hypothesis in this study. We also powered the analysis for the secondary hypotheses and used the repeatability investigation, which suggested a measurement error with a standard deviation of 0.16 mm for the sphere method when assessing the liTr by comparing a load of 3 kg with no load. Moreover, the pilot study revealed a population standard deviation of 1.09 mm for the liTr, suggesting a substantial biological variation in the liTr. Thus, it should be possible to estimate this variation and assess the effect of covariates. Based on our clinical findings, we expect to observe incidental findings of rotator cuff tears in two-thirds of asymptomatic shoulders in participants aged 45 years or older. Therefore, we expect to have 75 shoulders with rotator cuff tears. Within the 75 shoulders with rotator cuff tears, it will be possible to detect a difference of 0.8 mm in liTr with a power of 90%.

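### A power calculation at the analysis stage, run only for significant findings, cannot guard against chance findings, whichever effect size enters it

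*Protocol article*

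**What the plan says.** The point sits in the protocol article, Methods, Sample Size Calculation, in the paragraph after Figure 3.

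- **Status of the calculation:** "We adopted this sample size calculation post hoc after the aforementioned clinically relevant finding".
- **Status of the design:** "We kept the recruitment of 75 participants but adapted the study post hoc to 3 groups with 25 participants in each". The group structure and the calculation are post hoc; the planned number of participants is not.
- **Precaution:** "For any significant findings, this post hoc adaptation will be further investigated in the analysis stage by power calculation".
- **Purpose of the precaution:** "to assess potential limitations for the main analysis and reporting of results to avoid relying on findings by chance".

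The paragraph names no effect size for this calculation, no threshold, and no consequence of a low or high value.

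The design calculation just before Figure 3 reads: "For a 5% significance level, 90% power, and a correlation of 0.37, we need 76 shoulders", and then "Considering a possible dropout rate of 5%, we need 80 shoulders for the first hypothesis in this study". The same section gives the second planning effect, a 0.8 mm difference in load-induced translation (liTr) at 90% power.

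**The concern.** The authors disclose that the design was reshaped after the fact and want to protect readers from findings that arose by chance. That aim is sound, but the method does not match it. Power is the probability of a significant result given an assumed effect. It says nothing about whether a particular significant result is one of the false ones.

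The trigger adds to the problem. A check that runs only when a result is significant never looks at non-significant comparisons, where limited precision most needs to be shown.

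At stake is how the results are read. The Discussion expects recommendations from this study to bear on activity limits, treatment choice and rehabilitation. A power figure attached only to significant results could be taken as support for them when it carries no such information. This is a method the protocol states, with a purpose it states, so it is not a detail left to an analysis plan.

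**Working it through.** **1. The plan's own figure.** Inputs from Sample Size Calculation: r = 0.37, significance level 5% (two-sided assumed, since sidedness is not stated), power 90%, 76 shoulders, 5% dropout.

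- Simple approximation: n = (1.960 + 1.282)² / 0.37² = 76.75, so 76 or 77. This matches the stated 76.
- Fisher z: n = ((1.960 + 1.282) / atanh 0.37)² + 3, with atanh 0.37 = 0.3884, gives 72.6, so 73. On this formula, power at n = 76 is 91.3%.
- Dropout: 76 / 0.95 = 80.

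The stated 76 and 80 are consistent with the stated inputs and are not in dispute here.

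**2. First reading: power from the observed effect.** For a two-sided z-test with observed statistic z, where z is the normal quantile at 1 − p/2:

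observed power = Φ(z − 1.96) + Φ(−z − 1.96)

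The only input is p.

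| p | observed power |
|---|---|
| 0.05 | 50.0% |
| 0.03 | 58.3% |
| 0.01 | 73.1% |
| 0.005 | 80.2% |
| 0.001 | 90.8% |

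The floor is not peculiar to the z-test. At exactly p = 0.05, observed power is:

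- 50.2% to 51.6% for a correlation with n = 25, depending on the approximation, and 50.0% to 50.3% with n = 150;
- 50.4% for a two-sample t-test with 25 per group;
- 58.3% for a three-group F-test with 75 in total.

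In 4 million simulated z-tests with the null true, 5.0% were significant. Every one of those had observed power above 50%, with a median of 61%. For a given test and sample size the calculation therefore adds nothing to the p-value.

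**3. Second reading: power at the planning effect.** By Fisher z, with independent observations assumed:

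power = Φ(0.3884 × √(n − 3) − 1.96)

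- n = 25: Φ(1.822 − 1.960) = Φ(−0.138) = about 45%
- n = 50: Φ(2.663 − 1.960) = Φ(0.703) = about 76%
- n = 75: Φ(3.296 − 1.960) = Φ(1.336) = about 91%

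A variant with t critical values gives 45.7%, 76.6% and 91.2%. None of these figures uses the result of the study. A true positive and a false positive in the same comparison receive the same number, so the calculation cannot tell them apart.

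**4. The trigger.** On the second reading, the comparisons with about 45% power are the ones most likely to be non-significant even if the planning effect is real. Those are the comparisons that the rule leaves out.

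**The case against.** The strongest reply is that the protocol never speaks of observed power. What is to be investigated is the post hoc adaptation, and one stated purpose is to assess limitations. That can fairly be read as recomputing power for the achieved groups at the planning effect. Such power is not a function of p and can fall below 50%, as it does with 25 observations. It also has some bearing on false positives taken as a whole. If, purely for illustration, 20% of tested hypotheses were true, the share of significant results that are true would be 0.20 × 0.45 / (0.20 × 0.45 + 0.80 × 0.05) = 69% at 45% power, against 0.20 × 0.91 / (0.20 × 0.91 + 0.80 × 0.05) = 82% at 91% power. This stands: design power is a legitimate reason for general caution. It still cannot pick out a chance finding, and it gives no reason to run the calculation only after significance.

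Four stronger readings are tempting, and the document does not support them:

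- **That the check always returns more than 50%.** This holds only if the observed effect is used, which the protocol does not say.
- **That it would certify false positives as adequately powered.** No pass mark is set. Against the protocol's own 90% standard, only about 2.4% of significant results under the null would reach that level even with observed power, and about 10% would reach 80%. A cut-off of 80% would amount to a stricter significance level of about p < 0.005.
- **That the sample size was changed post hoc.** Recruitment stayed at 75.
- **That the lack of multiplicity control over the six secondary hypotheses is part of this defect.** That is a separate matter, commonly left to the statistical analysis plan, which is not shown.

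**Conclusion.** The concern holds. The protocol gives a power calculation the task of preventing reliance on chance findings, and it cannot perform that task under either reading. From the observed effect it restates p, with a floor of about 50% for any significant result. From the planning effect it gives about 45%, 76% or 91% according to the number of observations, whatever the truth of the finding. The conclusion therefore does not depend on the unstated effect size.

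The figures assume two-sided 5% tests. The design-power figures also assume independent observations; shoulders from the same person are correlated, so they are approximate.

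The step changes no endpoint, estimate, test or participant procedure, and the post hoc change is openly disclosed. It should be fixed because it affects how firmly results are claimed, but it does not undermine the study.

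**What to change.** - Delete the power calculation as a safeguard against chance findings.
- State that every result, significant or not, is reported with a 95% confidence interval and set against the planning effects in Sample Size Calculation: r = 0.37 for hypothesis 1 and the stated 0.8 mm difference in liTr.
- Label the contrasts that arose from the change to three groups as post hoc or exploratory.
- If a power figure is kept, compute it at the prespecified planning effect and the achieved group sizes, for all comparisons, and present it only as design sensitivity.

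The cost is a change of wording and slightly longer results tables. Claims from the post hoc contrasts become more cautious, which is what the authors say they want. No further recruitment or measurement is needed.

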### Ethics Approval

This study protocol was approved by the Ethics Committee Northwest Switzerland (2021-00182; Multimedia Appendix 2) and registered on ClinicalTrials.gov (NCT04819724). Prior to participation, written informed consent will be obtained from all participants. Participants can withdraw from the study at any time. This study is conducted in accordance with the Declaration of Helsinki, the principles of Good Clinical Practice, the Human Research Act, and the Human Research Ordinance, along with other locally relevant regulations.

### Safety Considerations

Fluoroscopy data will be used in this study to measure the glenohumeral translation. Fluoroscopy is a low-dose x-ray application routinely used in clinical practice. The estimated effective dose will be maximally 0.01 mSv. A standard x-ray of the chest, which is considered to have minimal radiation exposure, has an effective dose of 0.1 mSv and is comparable to exposure to 10 days of natural background x-ray volume [53]. To limit radiation exposure, fluoroscopy images will only be taken for 0-, 2-, and 4-kg handheld weights during the 30° abduction test in the scapular plane. Therefore, 1- and 3-kg handheld weights will not be included in the fluoroscopy-based liTr measurements.

## Results

Recruitment and data collection began in May 2021, and they will last until the recruitment target is achieved. Data collection is expected to be completed by the end of 2022. As of November 2022, data processing and analysis are in progress, and the first results are expected to be submitted for publication in 2023.

## Discussion

This experimental protocol will allow for a comprehensive analysis of clinical, functional, and biomechanical data. Furthermore, using MRI, asymptomatic rotator cuff tears will be revealed, aiding our understanding of the effect of rotator cuff tears on glenohumeral motion, especially in asymptomatic shoulders. We expect that rotator cuff tears will have a greater glenohumeral translation and that this will depend on the additional load applied and the anatomical parameters. In addition, a greater liMA of the deltoid muscle is expected with greater liTr. These outcomes might also be associated with muscle cross-sectional area, tear size, and type.

With our infrastructure, electromyographic/motion capture data and fluoroscopy images cannot be acquired simultaneously. Hence, we cannot completely rule out differences in the execution of the abduction tests. However, prior to data collection, exercises will be practiced, and verbal commands will be given to ensure comparable movements.

Glenohumeral translation is an important surrogate for shoulder instability that represents not only functional limitations but also a risk factor for the development of joint degeneration, including osteoarthritis. The results of this study will provide the first evidence of a dose-response relationship between additional weight and glenohumeral translation in patients with rotator cuff tears. Confirming this dose-response relationship and its impact on functional scores and modulating effects by tear type and size, muscle cross-sectional area, critical shoulder angle, and glenoid inclination will elucidate the importance of limiting additional weight during daily activity in this population. Revealing the effects of additional load on muscle activity of the intact rotator cuff tendon in the injured joint will provide evidence of potential overload in these muscles that may lead to secondary damage in other tissues in the injured joint. This study can be considered a proof of concept of a potential diagnostic test (loading shoulder abduction test) for glenohumeral translation. The recommendation based on our results will directly impact activity limitations in patients with rotator cuff tears and influence treatment choice and rehabilitation regimens. The results of this study will be presented at national and international conferences and published in peer-reviewed open-access journals.

## Appendix

Multimedia Appendix 1 SPIRIT (Standard Protocol Items: Recommendations for Intervention Trials) checklist.

Multimedia Appendix 2 Ethics approval.

Multimedia Appendix 3 External funder confirmation.

Multimedia Appendix 4 External peer-review report by the Swiss National Science Foundation.

## Abbreviations

DASH: Disabilities of Arm, Shoulder, and Hand
liMA: load-induced changes in muscle activation
liTr: load-induced glenohumeral translation
MRI: magnetic resonance imaging
REDCap: Research Electronic Data Capture
SENIAM: Surface ElectroMyoGraphy for the Non-Invasive Assessment of Muscles
SPIRIT: Standard Protocol Items: Recommendations for Intervention Trials
TSE: turbo spin echo
